## Abstract

**Background:**

Evidence shows that computerized self-help interventions are effective for reducing symptoms of depression. One such intervention, SPARX, is a gamified mobile computerized cognitive behavioral therapy (cCBT) developed for adolescents in New Zealand, which was shown to be as effective as usual care for young people with mild-to-moderate symptoms of depression. However, gamified cCBT has not yet been tested in Japan.

**Objective:**

This trial is designed to investigate whether a Japanese-adapted version of SPARX improves depressive symptoms in Japanese university students with mild-to-moderate depressive symptoms.

**Methods:**

In this 7-week, multicenter, stratified, parallel-group, superiority randomized trial, participants will be allocated to either a treatment condition (SPARX) or a wait-list control condition. SPARX is a fully automated program, which will be delivered to the mobile phone or tablet device of the participants. SPARX is designed as an interactive fantasy game to guide the user through seven modules that teach key CBT strategies. All participants will be recruited from universities via advertisements on online bulletin boards, the campus newspaper, and posters. Participants in the treatment condition will use the SPARX program weekly. The primary outcome is the reduction of depressive symptoms (using Patient Health Questionnaires-9) measured at baseline and weekly: once after the 7-week intervention and once at a 1-month follow-up. Secondary outcomes include satisfaction with the program and satisfaction with life, measured by the Satisfaction With Life Scale; positive and negative moods, measured by the Profile of Mood States Second Edition; social functioning, measured by the EuroQol Instrument; rumination, measured by the Ruminative Responses Scale; and coping, measured by the Brief Coping Orientation to Problem Experienced Inventory.

**Results:**

This study received funding from The Research Institute of Personalized Health Sciences, Health Sciences University of Hokkaido, and obtained institutional review board approval in September 2019. Data collection began in April 2019.

**Conclusions:**

Results of this trial may provide further evidence for the efficacy of gamified cCBT for the treatment of depression and, specifically, provide support for using SPARX with Japanese university students.

**Trial Registration:**

Japan Primary Registries Network UMIN000034354; https://tinyurl.com/uu7xd77

**International Registered Report Identifier (IRRID):**

DERR1-10.2196/15164

## Introduction

### Background

Depression is a mental health problem commonly experienced by university students. A systematic review examining rates of depression among university students from a range of countries, including North American, European Union, East Asian, and Middle Eastern countries, revealed the weighted mean prevalence rate of depressive disorders of 30.6% [1], which is considerably higher than that reported for the general population (6.6%) [2]. Depression and other mental health concerns such as anxiety and stress negatively impact academic performance [3-5], which may result in students dropping out of university [6] and potentially affect their future career prospects. For example, in Japan, only 1.7% of individuals that dropped out of university reported eventually working as full-time permanent employees for three or more years, whereas 60% of university and graduate school graduates obtained regular employment [7]. Therefore, the mental well-being of tertiary students is not only a health care issue but also an issue that influences the overall socioeconomic welfare of a society.

In Japan, 126 of the 135 universities (93%) have some established support systems to address the mental health needs of university students [8]. However, reaching out to professional mental health services among students is relatively uncommon [9,10] owing to several factors, including skepticism about treatment effectiveness, lack of awareness of help options, and lack of perceived need [11,12]. Therefore, access to university mental health services should be adjusted so that it is both easier and more acceptable [13]. Outside Japan, there have been many trials of internet-based and computer-delivered interventions in recent years, demonstrating significant improvements in depression compared to an inactive control (pooled standardized mean difference –0.43, 95% CI –0.63 to –0.22) [14]. Digital interventions offer important advantages: they are accessible from various locations, they can be a form of outreach to individuals who might not otherwise access traditional face-to-face services [15,16] and are more cost-effective than face-to-face treatment [17]. Moreover, digital interventions can facilitate learning and retention because users can return to the program at their convenience to practice the content more than once [18]. Given that games are familiar and particularly popular with young people in Japan [19,20], game-based interventions have the potential to be engaging and valuable self-help tools to support university students’ mental health [21,22].

In earlier studies, a variety of game-based interventions for mental health suggested potential benefits for mental and physical symptoms [23-25]. At present, the Smart, Positive, Active, Realistic, X-factor thoughts (SPARX) program [26] is the only available game-based intervention developed to specifically deliver cognitive behavioral therapy (CBT) for adolescent users with depressive symptoms [22,27]. SPARX was created, evaluated, and implemented nationally in New Zealand for use by adolescents with mild-to-moderate depressive symptoms [26]. Furthermore, SPARX was used as a depression prevention intervention in a large Australian school trial to reduce depressive symptoms in adolescents prior to final year examinations [28]. In Japan, a smartphone-based CBT program (Kokoro-app) was demonstrated to be effective for depression in a clinical sample [29]; however, there have been no trials of game-based CBT for depression in Japanese university students conducted to date. It is anticipated that SPARX may be well received by university students experiencing depressive symptoms who do not have contact with professional services. However, a formal randomized controlled trial (RCT) is warranted to establish whether SPARX is effective in this population.

### Objectives

The primary objective of this trial is to examine whether SPARX improves depressive symptoms in Japanese university students who present mild-to-moderate symptoms. We hypothesize that SPARX will be more effective for improving depressive symptoms than a wait-list condition. In the systematic review of trials of internet-based and computer-delivered interventions for university students [14], although half of the included trials used an inactive control group (wait-list or no treatment), the other half used an active control (eg, attention training or providing educational information on anxiety and depressive disorders). This will be the first clinical trial of SPARX for university students in Japan. Therefore, we will examine the difference between a SPARX group and a wait-list control group.

The secondary objectives are to determine whether SPARX delivered to Japanese students with mild-to-moderate depressive symptoms leads to (1) enhanced positive mood and reduced negative mood, (2) improved satisfaction with life, (3) improved health-related quality of life, (4) reduced depressive rumination, and (5) improved coping skills.

## Methods

### Study Design

This is a multicenter trial and follows a stratified randomized, parallel-group superiority design. Participants will be randomized 1:1 to an intervention arm, which will consist of the game-based computerized CBT program SPARX or a wait-list control condition. Postintervention assessments will be carried out 7 weeks after baseline assessment. The participant flow through the trial is shown in Figure 1.

**Figure 1 figure1:**
[figure not shown]
Participant flow of this trial. CES-D: Center for Epidemiological Studies Depression; SPARX: Smart, Positive, Active, Realistic, X-factor thoughts.

### Setting

This multicenter study will be conducted at three universities: Health Sciences University of Hokkaido, Hokusho University, and Ritsumeikan University. We plan to recruit participants from April 2019 through March 2020.

### Participants

A total of 100 participants will be sought to take part in this trial. Participants will be included in the trial if they meet the following inclusion criteria at the face-to-face or telephone eligibility interview: (1) mild-to-moderate depressive symptoms on the Center for Epidemiological Studies Depression Scale (CES-D) [30] with scores between 16 and 24 [31,32], (2) age of 18-30 years, (3) attending one of the participating universities, and (4) owning and being able to use a smartphone/tablet device. These inclusion criteria differ from those of the first SPARX study [26]. Namely, we include university students aged 18-30 years instead of high school students, who were recruited for the first SPARX study [26], because when the Japanese version of SPARX was first developed, this app was designed with adult users in mind, including university students, rather than high school students. In addition, we decided to conduct the current study based on the contemporary reality of Japanese university students, because a study conducted by the Ministry of Education, Culture, Sports, Science and Technology of Japan in 2018 [33] found that Japanese university students aged 18-30 years accounted for approximately 99.9% of the total university students in Japan.

Participants will be excluded if they have: (1) high risk of self-harm or suicide at study entry based on a self-report; (2) severe depressive symptoms, as indicated by a CES-D score>24 [31,32]; (3) current manic episodes or current schizophrenia or other psychotic disorders at baseline as reported by a participant; (4) previous experience of using SPARX; and (5) involvement in manualized psychotherapy at baseline. These exclusion criteria are the same as those adopted in the first SPARX study [26] as reference. Merry et al [26] suggested that people exhibiting severe depressive symptoms or at high risk of self-harm or suicide should be excluded because they could not provide a self-help resource as a viable option. In addition, individuals experiencing current manic episodes, schizophrenia, or other psychotic disorders, or are involved in manualized psychotherapy at baseline were excluded because they require medical and psychiatric treatment suitable for their symptoms rather than SPARX or are already receiving suitable psychiatric treatment. If we do not reach the sample size required to test the primary hypothesis of this study, we will extend recruitment to other interested universities and will consider using online recruitment.

### Clinical Safety Procedures

For participants indicating a high risk of self-harm or suicide at screening and at any time during this trial, the researchers will provide information on available mental health care services that the participants can access and will ask the participant to cease participation in this trial. However, participants will be provided with ongoing access to SPARX even if they decide to withdraw from the trial. In relation to ancillary care, the participants will be allowed to contact the researchers at any point during the trial. If any event requiring additional care occurs, a researcher will inform the individual at the contact address or telephone number of the appropriate medical or psychological care and mental health service as provided by the participant’s health insurance.

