### Study Procedure

All participants will be recruited from the abovementioned universities via advertisements on online bulletin boards, campus newspapers, and posters. Interested students who contact the researchers via email will be provided with further information related to the study and will be given time to consider their participation. If interested, they will be screened using Google forms (developed by the authors for this study) for eligibility using the Japanese version of the CES-D [30]. The cutoff score of CES-D was verified in Japanese samples [30]. If the score is 16-24, the researcher will continue with the eligibility interview to confirm that all other criteria are met. At the end of the interview, written consent will be obtained. Those who score less than 15 or above 25 will be excluded from the trial but will be provided with free access to SPARX, according to the needs of the participant. Those whose score is 25 or more, indicating severe depressive symptoms [31,32], will be provided with information about available mental health care services.

For participants in the treatment condition, SPARX will be delivered on their mobile phone or tablet device. They will be asked to play the SPARX program weekly at a designated university location (eg, a vacant laboratory or conference room) with one of the researchers (or a research assistant) present in another room (eg, a neighboring laboratory) for the purpose of checking SPARX use and being available to answer any questions from the participant. Each weekly session with SPARX is expected to take about 30 min.

Participants in the wait-list condition group will receive access to SPARX after a 1-month follow-up assessment of the treatment condition group. They will be asked to fill out assessments at the same time as the assessments of the treatment condition group at experimental laboratories, in conference rooms at each university, or on online Google forms. They will not be granted access to SPARX until all assessments have been completed.

To address potential issues of contamination, we forbid participants from talking about any theme of SPARX, such as the use of SPARX and any impressions of this study, during trial participation because other students in their university campus are participating in the current trial.

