### Measures

The primary outcome (Japanese version of PHQ-9) will be measured at baseline (T1), weekly throughout the interventions (T2-T7), at postassessment 1 week after the 7 intervention weeks (T8), and at 1-month follow-up (T9). Other assessments will be conducted at preassessment (T1), postassessment (T8), and 1-month follow-up (T9). Table 1 shows the schedule of assessments at various time points. At baseline (T1), demographics data will be collected, including gender, age, major in university, year of study, residence status; presence or absence of visits to psychiatric and counseling services; and presence or absence of the use of a gamified psychological program.

**Table 1 table1:** Overview of measurements.

Outcome	Scale	T1^a^	T2-T7^b^	T8^c^	T9^d^
Demographics	Developed by the authors	✓			
Depressive symptoms	PHQ-9^e^	✓	✓	✓	✓
Satisfaction with life	SWLS^f^	✓		✓	✓
Negative and positive moods	POMS-2^g^	✓		✓	✓
Social functions	EQ-5D^h^	✓		✓	✓
Rumination	RSS^i^	✓		✓	✓
Coping	Brief COPE^j^	✓		✓	✓
Stressor	DLSS^k^	✓		✓	✓
Satisfaction and acceptability	Developed by the authors				✓

^a^T1: baseline assessment (preassessment).

^b^T2-T7: assessment at each level.

^c^T8: assessment 1 week after the program.

^d^T9: assessment at 1-month follow-up.

^e^PHQ-9: Japanese version of Patient Health Questionnaire-9.

^f^SWLS: Satisfaction With Life Scale.

^g^POMS-2: Profile of Mood Scale, second edition.

^h^EQ-5D: Japanese EuroQol instrument.

^i^RSS: Japanese version of the Ruminative Responses Scale.

^j^Brief COPE: Brief Coping Orientation to Problem Experienced inventory.

^k^DLSS: Daily Life Stress Scale for undergraduates.

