### Statistical Analyses

The analysis for primary outcome measures will be conducted using a linear mixed model (LMM). The LMM approach was selected because of its strength in accommodating missing data and its ability to incorporate random effects into analyses. In these analyses, the dependent variable is the PHQ-9 score, and the independent variables are assignment (treatment condition, wait-list condition) and time [preassessment (T1), each session assessment (T2-T7), post-assessment (T8), and follow-up assessment (T9)], with interaction of the assignment and time as fixed-effect variables and participants as a random-effects variable. Secondary outcomes (outcome measures, process measures, and evaluation of the program) will be analyzed in the same way as the primary outcome. Subgroup analyses are not planned. For all analyses, *P*<.05 will be inferred as statistically significant. Up-to-date versions of R software (R Foundation for Statistical Computing, Vienna, Austria) will be used to analyze the quantitative data.

In the satisfaction/acceptability measure, free comments will be analyzed using thematic analysis.

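### Participants who become high risk are asked to leave the trial and no further PHQ-9 collection is stated: a risk of informative missingness, of unknown direction and probably small size

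*Protocol article*

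**What the plan says.** The rule in the Protocol article, Clinical Safety Procedures, applies "For participants indicating a high risk of self-harm or suicide at screening and at any time during this trial". The researchers give information on care services and "will ask the participant to cease participation in this trial". The same paragraph adds that "participants will be provided with ongoing access to SPARX even if they decide to withdraw from the trial". No section says whether PHQ-9 forms are still collected from these participants, and none says that scores already collected are discarded.

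Under Measures, the PHQ-9 is scheduled at T1, weekly at T2 to T7, one week after the program (T8) and at one month (T9). The Results section places the primary outcome at the one-month follow-up. Statistical Analyses specifies a linear mixed model over all nine time points with a participant random effect, chosen "because of its strength in accommodating missing data".

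Study Procedure describes different contact in the two arms. SPARX participants attend weekly on campus "with one of the researchers (or a research assistant) present in another room". Wait-list participants complete assessments in laboratories, "in conference rooms at each university, or on online Google forms". Of the wait list it says: "They will not be granted access to SPARX until all assessments have been completed".

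**The concern.** Removal at screening happens before randomization and does not affect the comparison. Removal after randomization does. Because SPARX stays available, the rule as written ends a person's part in the trial, and with it apparently the measurement, rather than access to the intervention. Its trigger is closely related to what the PHQ-9 measures. The participants who lose their T8 and T9 values are therefore likely to include some of those doing worst.

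A likelihood-based mixed model is valid under dropout if the recorded scores explain who leaves. A deterioration between two weekly forms, or in the month between T8 and T9, can lead to departure before any score captures it. What is at stake is the treatment contrast at the end of follow-up. Scores that were never collected cannot be recovered at analysis.

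**Working it through.** **1. The plan's own figure.** Inputs from Sample Size: d = 0.60, two-sided alpha 0.05, power 0.80, 10% dropout.
- Normal formula: n per arm = 2(1.960 + 0.842)²/0.60² = 43.6, so 44 per arm (88).
- t-test version: 44.6, so 45 per arm (90), with power 0.804.
- Inflation: 90/(1 − 0.10) = 100.

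The stated 90 and 100 reproduce. Nothing is wrong with them.

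**2. Direction, in closed form.** Assumption: T9 scores have unit SD, with mean 0 in controls and −0.60 under SPARX, and every score above a cut-off c is lost. The observed mean in an arm with mean μ is μ − φ(c − μ)/Φ(c − μ). With 5% of controls lost, c = 1.645:
- controls: −0.103/0.950 = −0.109
- SPARX: −0.600 − 0.032/0.988 = −0.633
- difference: 0.524

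With 2%, 5%, 10% and 15% of controls lost, the available-case effect is 0.56, 0.52, 0.48 and 0.44. If instead all high scores are detected in the SPARX arm but only 0% to 25% of them in the wait list (5% to 15% of controls being above the cut-off), the effect is 0.61 to 0.71. With no true effect and equal detection, both arms lose the same part of the same distribution and no bias arises.

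**3. What the planned model does with weekly data.** Assumptions: 40,000 per arm; nine visits; unit variance, made up of 0.4 shared, 0.5 × 0.7^lag and 0.1 residual; effect rising linearly to 0.60 at T8 and held at T9; departure from T2 on when a score exceeds 2.4, 2.0 or 1.6. Simulation error of the T9 difference is about √(2/40,000) = 0.007.

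| Wait-list detection | Triggering score recorded | Missing at T9, control / SPARX | Available cases | Random-intercept model |
|---|---|---|---|---|
| equal | yes | 3.6% / 1.5% | 0.568 | 0.597 |
| equal | yes | 8.9% / 4.7% | 0.537 | 0.585 |
| equal | yes | 18.5% / 10.8% | 0.510 | 0.589 |
| equal | no | 4.3% / 1.8% | 0.561 | 0.588 |
| equal | no | 9.9% / 4.8% | 0.537 | 0.584 |
| equal | no | 20.0% / 11.1% | 0.486 | 0.553 |
| 30% of SPARX | yes | 1.4% / 1.6% | 0.591 | 0.585 |
| 30% of SPARX | yes | 3.9% / 4.4% | 0.611 | 0.599 |
| 30% of SPARX | yes | 8.6% / 11.1% | 0.613 | 0.571 |
| 30% of SPARX | no | 1.7% / 1.8% | 0.596 | 0.594 |
| 30% of SPARX | no | 4.3% / 4.7% | 0.617 | 0.613 |
| 30% of SPARX | no | 9.8% / 11.3% | 0.608 | 0.596 |

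The mixed model recovers most of what available cases lose. Its estimates run from 0.55 to 0.61, and the highest, 0.613, is within two simulation errors of 0.60.

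**4. A harsher set-up.** Individual trajectories diverge (random slopes, SD 0.5 or 1.0), detection is equal and the triggering score is never recorded (200,000 per arm). With 5.3% and 7.8% of controls removed, the T9 estimates are 0.581 and 0.551. With 13.2% and 16.6% removed, they are 0.567 and 0.521.

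**The case against.** Much can be said for the plan. Participants are only asked to leave. The PHQ-9 is collected weekly, so the deterioration behind a departure may well be on record, and the mixed model then uses it: 0.585 to 0.597 under equal detection. Entry is limited to CES-D 16 to 24 and excludes high risk at entry, so nothing in the article supports the higher removal rates above. The 10% dropout allowance does not exclude these withdrawals and may already cover them. A condensed article may also leave follow-up after withdrawal to the full protocol. All of this stands as regards size. It does not remove the point, because the article states a rule that ends trial participation on an outcome-related trigger and sets nothing beside it to keep measurement going.

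A reader might infer something stronger: that the worst scores are deleted, that the effect is pulled toward zero, and that power falls to about 70%. The documents support none of the three.
- **Deleted.** Scores recorded before departure are not said to be removed and can enter the model. Only later ones are lost.
- **Toward zero.** This needs a real benefit and equal detection. The SPARX arm is on campus weekly with a researcher nearby, while the wait list may answer online, so detection may differ.
- **Power of 70%.** The arithmetic is correct but the inputs are chosen. Taking 4% and 7.8% removals on top of the full dropout allowance leaves 45 × 0.96 = 43.2 and 45 × 0.922 = 41.5 per arm, and d = 0.55 then gives 0.705. At d = 0.60 the same numbers give 0.778, and d = 0.58 with 45 per arm gives about 0.78. Most of the fall comes from choosing 0.55. It is also a single-time-point t-test figure, not the power of the planned repeated-measures model.

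**Conclusion.** The point holds in a limited form. The rule creates an avoidable risk that T8 and T9 scores are missing for a reason tied to the primary outcome, and the mixed model corrects this only in part. The direction is unknown: toward zero with a true benefit and equal detection, possibly away from zero if risk is detected more often in the SPARX arm. The size is probably small. Under assumed rates the mixed-model estimate was 0.55 to 0.61 SD against 0.60, with 0.52 in the harshest case. Thresholds, correlations, detection and event rates are all assumptions. The article gives no event rate, so no bias or power figure can be attached to this trial. It is a cheap improvement, not a flaw that threatens the trial.

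**What to change.** In Clinical Safety Procedures, leave the safety response unchanged and add that it is separate from outcome assessment. Unless consent is withdrawn, participants in either arm to whom the rule applies after randomization are invited to complete the remaining PHQ-9 assessments, at least T8 and T9, on the online form already used for wait-list assessments. Keep all their recorded scores in the primary model, and report the number of such events by arm.

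The same edit should reconcile two sentences. The continued-access sentence in Clinical Safety Procedures covers participants without naming an arm, while Study Procedure gives the wait list no access before all assessments are done. The text does not settle which applies to a wait-list participant who leaves early, and this affects how that person's later scores are read.

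Cost: about one sentence in the protocol and consent form, an ethics notification and a few extra online forms. The real downside is limited further contact with distressed participants, who may decline. The article reports enrollment as ongoing, so the change could still help those not yet finished.
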